## 4. STUDY DRUG ADMINISTRATION PROCEDURES

### 4.1. Patient Assignment and Blinded Administration

Patients who meet all entry criteria and present no exclusion criteria will be randomised to receive either pyronaridine artesunate (plus matching placebo of chloroquine) or chloroquine (plus matching placebo of pyronaridine artesunate) in a 1:1 ratio according to the randomisation scheme provided by the Sponsor or designee. The randomisation scheme will be generated using permutation blocks technique. Complete blocks will be assigned to each study site. Patients will be assigned, in ascending order, a randomisation number according to the order recruited. The patient will be allocated an individual numbered treatment pack which contains sufficient tablets for 3 days therapy plus an overage bottle containing tablets in case the patient vomits the first dose.

The Investigator will measure the patient's body weight at entry and refer to the chart (Attachment 4) to calculate the actual number of tablets to be administered daily.

Patients will be allocated the following identification nomenclature according to the order recruited within a given site: **site code-patient number**.

Clinical trial material will be administered using a double blind design. That is: neither the Investigator neither the patient will be aware of the treatment arm to which the patient has been assigned.

### 4.2. Materials and Supplies

#### 4.2.1. Study drug: pyronaridine artesunate or matching placebo

Pyronaridine artesunate and its matching placebo will be supplied by Shin Poong Pharm Co. Ltd in high density polyethylene bottles as numbered individual treatment allocations. The active ingredients of the investigational product are pyronaridine tetraphosphate and artesunate.

The tablet strength to be used is 180:60 mg pyronaridine artesunate. Depending on their body weight, patients will receive between 1 to 4 tablets per day (see Attachment 4). The actual dose-level range covered by this regimen is between 7.2:2.4 mg/kg and 13.8:4.6 mg/kg pyronaridine artesunate, respectively.

Pyronaridine artesunate and its matching placebo clinical trial material will be packaged in 3 bottles corresponding to each dosing day and each containing 4 tablets. Unused tablet shall be kept in their original packaging and remain the Investigators' responsibility for drug accountability. A fourth bottle will be provided as an overage of one day's supply, in the event a patient requires re-dosing due to vomiting the first day's treatment (Day 0). According to the randomization list, the tablets will contain either active drug or a placebo with matching aspect, color and taste.

Example Product Label for pyronaridine artesunate:

|                                                                                                                                                                                                                                                                                                                                                                                                                                                                                                                |
|----------------------------------------------------------------------------------------------------------------------------------------------------------------------------------------------------------------------------------------------------------------------------------------------------------------------------------------------------------------------------------------------------------------------------------------------------------------------------------------------------------------|
| 
Product for Clinical Study Use ONLY
 
Study Reference: SP-C-006-06
 
Patient number:
 
Study Visit: Day 0 (1 or 2 or Overage)
 
Contains: 4 Tablets
 
Each tablet contains:
 
pyronaridine 180 mg / artesunate 60 mg or matching placebo
 
Storage: Below 30 degrees C
 
Lot No.:
 
Expiration date:
 
To be administered by Study Staff only
 
Sponsor: SHINPOONG PHARM. Co., Ltd., Republic of Korea
 |
|----------------------------------------------------------------------------------------------------------------------------------------------------------------------------------------------------------------------------------------------------------------------------------------------------------------------------------------------------------------------------------------------------------------------------------------------------------------------------------------------------------------|

#### 4.2.2. Chloroquine or matching placebo

The comparator drug chloroquine and its matching placebo will be supplied by Shin Poong Pharm Co. Ltd. Clinical trial material will be presented in high density polyethylene bottles as numbered individual treatment allocations.

The dosage to be used for adults is 620 mg chloroquine on Days 0 and 1 and 310 mg on Day 2. The tablet strength to be used is 155 mg chloroquine base, which

will provide a posology for adults of 4 tablets on Days 0 and 1 and 2 tablets on Day 2. The dosage to be used for children is 10 mg/kg chloroquine base (i.e. between 1 and 3 tablets, depending on the child's weight) on Days 0 and 1 and 5 mg/kg (i.e. between 0.5 and 1.5 tablets depending on the child's weight) on Day 2. The dosage should not exceed the adult dose regardless of weight (see Attachment 4).

Chloroquine and its matching placebo clinical trial material will be packaged in 3 bottles corresponding to each dosing day. The bottles for Day 0 and 1 will contain 4 tablets, while the bottle for Day 2 will contain 2 tablets. Unused tablets of chloroquine or matching placebo shall be kept in their original packaging and remain under the Investigator's responsibility for drug accountability. A fourth bottle containing 4 tablets will be provided as an overage of the first day's supply, in the event a patient requires re-dosing due to vomiting the first day's treatment (Day 0). According to the randomization list, the tablets will contain either active drug or a placebo with matching aspect, color and taste.

Example Product Label for chloroquine:

|                                                                                                                                                                                                                                                                                                                                                                                                                                                               |
|---------------------------------------------------------------------------------------------------------------------------------------------------------------------------------------------------------------------------------------------------------------------------------------------------------------------------------------------------------------------------------------------------------------------------------------------------------------|
| 
Product for Clinical Study Use ONLY
 
Study Reference: SP-C-006-06
 
Patient number:
 
Study Visit: Day 0 ( or 1 or Overage)
 
Contains: 4 Tablets
 
Each tablet contains:
 
chloroquine base 155 mg or matching placebo
 
Storage:
 
Lot No.:
 
Expiration date:
 
To be administered by Study Staff only
 
Sponsor: SHINPOONG PHARM. Co., Ltd., Republic of Korea
 |
|---------------------------------------------------------------------------------------------------------------------------------------------------------------------------------------------------------------------------------------------------------------------------------------------------------------------------------------------------------------------------------------------------------------------------------------------------------------|

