|                                   | 
orally. Patients will receive:
For adults: 620 mg (i.e. 4 tablets) on Days 0 and 1 and 310 mg (i.e. 2 tablets) on Day 2.
For children: 10 mg/kg on Days 0 and 1 and 5 mg/kg on Day 2.
                                                                                                                                                                                                                                                                                                                                                                                                                                                                                                                                                                                                                                                                                                                                                                                                                                                                                                                                                                                                                                                                                                                                                   |

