| Concomitant Treatment      | 
The administration of paracetamol/acetaminophen (<math>\leq 1</math> g) on Day 0, 1 and 2 is allowed if the patient's condition warrants it and should be recorded in the appropriate section of the CRF.
 
Rescue treatment: Treatment failures will be treated with best antimalarial therapy available in the country where the study is conducted.
 
If during follow-up, infections other than malaria require the administration of drugs with antimalarial activity (such as co-trimoxazole, tetracycline or doxycycline), the patient will be considered a protocol violator, with the exception of patients given tetracycline as eye ointment.
 
All concomitant medications taken by the patient during the study, from the date of signature of the informed consent will be recorded in the appropriate section of the CRF.
                                                                                                                                                            |
| Study Drugs Administration | 
Study drug will be administered orally once a day for three consecutive days, i.e. on Days 0, 1 and 2, by authorized member of the investigation team.
 
Depending on their body weight, patients will receive a total of between 2 to a maximum of 8 tablets per day on Days 0 and 1 and a total of between 1.5 to a maximum of 6 tablets per day on Day 2.
                                                                                                                                                                                                                                                                                                                                                                                                                                                                                                                                                                                                                                                  |

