#### Choice of comparator

In spite of the increasing numbers of resistant strains, chloroquine monotherapy is still recommended as standard blood-stage therapy for patients with *P. vivax* malaria in the countries in which this trial will be conducted. Its selection as comparator is therefore justified. The adult dose of chloroquine will be 620 mg for 2 days followed by 310 mg on the third day and for children 10 mg/kg for the first two days and 5 mg/kg for the third day. Total dose is in accordance with the current practice in the countries where the study is conducted. The safety profile of chloroquine is well established and known. Although generally well tolerated, the following side-effects of chloroquine treatment have been described:

Gastro-intestinal disturbances, headache, hypotension, convulsions, visual disturbances, depigmentation or loss of hair, skin reactions (rashes, pruritus) and, rarely, bone-marrow suppression and hypersensitivity reactions such as urticaria and angioedema. Their occurrence during the present trial may however be unlikely given the short (3-day) duration of treatment.

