##### 3.2.1. Inclusion criteria

Patients must fulfil the following inclusion criteria to be eligible for enrolment in the study:

1. Male or female patients between the age of 3 and 60 years, inclusive.
2. Body weight between 20 kg and 90 kg with no clinical evidence of severe malnutrition.
3. Presence of acute uncomplicated *P. vivax* mono-infection confirmed by:

- a. Fever, as defined by axillary/tympanic temperature  $\geq 37.5^{\circ}\text{C}$  or oral/rectal temperature  $\geq 38^{\circ}\text{C}$ , or history of fever in the previous 24 hours (history of fever must be documented) **and**,
  - b. Positive microscopy of *P. vivax* with parasite density  $\geq 250/\mu\text{L}$  of blood (including at least 50% of asexual parasites)
4. Written informed consent, in accordance with local practice, provided by patient and/or parent/guardian/spouse. If the patient is unable to write, witnessed consent is permitted according to local ethical considerations.
5. Ability to swallow oral medication.
6. Ability and willingness to participate based on information given to patient or parent or guardian and access to health facility.

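### The stated child chloroquine dose of 10/10/5 mg/kg is not what the dosing chart gives at 20-23 kg: that row is 22.5-32.6% lower on every day

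*Protocol*

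**What the plan says.** The child chloroquine dose appears in three places, each time as fixed mg/kg values with no tolerance or delivered range.

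- Section 4.2.2, Days 0 and 1: "The dosage to be used for children is 10 mg/kg chloroquine base (i.e. between 1 and 3 tablets", depending on weight. Day 2: "5 mg/kg (i.e. between 0.5 and 1.5 tablets", again by weight.
- Synopsis, Study Drugs & Comparator: "For children: 10 mg/kg on Days 0 and 1 and 5 mg/kg on Day 2".
- Introduction, Choice of comparator: "for children 10 mg/kg for the first two days and 5 mg/kg for the third day". The same paragraph adds that the total dose agrees with current practice in the participating countries.

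The tablets given are set elsewhere. Section 4.1 tells the investigator to weigh the patient and "refer to the chart (Attachment 4) to calculate the actual number of tablets to be administered daily". The first row of the chloroquine child table in Attachment 4 covers 20-23 kg and gives 1 tablet on Days 0 and 1 and 0.5 tablet on Day 2. The tablet is 155 mg base. Entry requires "Body weight between 20 kg and 90 kg with no clinical evidence of severe malnutrition", so this row applies to eligible patients.

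The investigational drug is described differently. Section 4.2.1 prints what its chart delivers: "The actual dose-level range covered by this regimen is between 7.2:2.4 mg/kg and 13.8:4.6 mg/kg pyronaridine artesunate".

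**The concern.** Section 4.2.2 treats a mg/kg dose and a tablet range as two descriptions of the same regimen. At the bottom of the range they are not the same. Ethics committees, regulators and later readers are told 10/10/5 mg/kg; a child of 20-23 kg receives roughly 7 mg/kg on each of the first two days and 3.5 mg/kg on the third.

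The drug concerned is the active comparator in a non-inferiority trial with a 10-point margin on Day 14 cure. The result is read against chloroquine at its stated regimen, and the Introduction justifies the comparator partly on its total dose. If a lower dose cures fewer patients, the shortfall would help the new drug within that weight band.

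**Working it through.** **Inputs.** Tablet strength 155 mg base (section 4.2.2); stated doses 10 and 5 mg/kg (section 4.2.2, Synopsis, Introduction); tablet counts by weight (Attachment 4); minimum weight 20 kg (section 3.2.1). The stated three-day total, 10 + 10 + 5 = 25 mg/kg, is my sum; the protocol does not print it.

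**Check of the method.** Dose per kg = tablets x strength / weight, taken at the ends of each band in whole kilograms. On the pyronaridine chart this gives 180/25 = 7.2 and 360/26 = 13.8 mg/kg, which is the range printed in section 4.2.1. Reading the bands as whole kilograms therefore matches the protocol's own practice.

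**Check that the row is as intended.** The lower ends of the tablet ranges in section 4.2.2 (1 and 0.5) match it. So does the Synopsis, which gives "a total of between 1.5 to a maximum of 6 tablets per day on Day 2": at the lowest weight, 1 pyronaridine artesunate tablet + 0.5 chloroquine tablet = 1.5. The row is not a misprint or an extraction fault.

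**Delivered dose, 20-23 kg.**
- Days 0 and 1: 155/20 = 7.75 and 155/23 = 6.74 mg/kg. Against 10: -22.5% and -32.6%.
- Day 2: 77.5/20 = 3.88 and 77.5/23 = 3.37 mg/kg. Against 5: -22.5% and -32.6%.
- Total: 2.5 x 155 = 387.5 mg; 387.5/20 = 19.4 and 387.5/23 = 16.8 mg/kg. Against 25: -22.5% and -32.6%.

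**Where the stated dose would be met.** One tablet is 10 mg/kg at 155/10 = 15.5 kg, and half a tablet is 5 mg/kg at 77.5/5 = 15.5 kg. No eligible child weighs that little.

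**Does half-tablet rounding explain it?** 10 mg/kg needs 200/155 = 1.29 to 230/155 = 1.48 tablets, so the nearest half tablet is 1.5 throughout the band and the chart gives 1. On Day 2, 5 mg/kg needs 100/155 = 0.65 to 115/155 = 0.74 tablets, and 0.5 is the nearest. Rounding accounts for Day 2 only.

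**All child rows, at the lower and upper weight of each band (mg/kg; total compared with 25):**

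| Weight (kg) | Days 0-1 | Day 2 | Total |
|---|---|---|---|
| 20-23 | 7.75 to 6.74 | 3.88 to 3.37 | 19.4 to 16.8 (-22.5% to -32.6%) |
| 24-27 | 9.69 to 8.61 | 6.46 to 5.74 | 25.8 to 23.0 (+3.3% to -8.1%) |
| 28-38 | 11.07 to 8.16 | 5.54 to 4.08 | 27.7 to 20.4 (+10.7% to -18.4%) |
| 39-40 | 11.92 to 11.63 | 5.96 to 5.81 | 29.8 to 29.1 (+19.2% to +16.3%) |

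Only the first row lies below the stated dose on all three days across its whole band. The other rows reach or pass it on some day or at some weight.

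**The case against.** The arithmetic is not in dispute. The case for leaving the text alone is that nothing can go wrong at the bedside. Sections 4.1, 4.5 and 5.2.1.2 all tie the tablet count to screening weight, and Attachment 4 is unambiguous for a child of 20-23 kg. Weight-band dosing never hits a mg/kg target exactly, and pyronaridine is also in the lowest third of its printed range here: 180/20 = 9.0 to 180/23 = 7.8 mg/kg, within 7.2 to 13.8. Most of this stands. The fault is a false dose statement, not a risk of misdosing. It does not excuse Days 0 and 1, where a half tablet more would have been closer to target.

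A reader might infer that the comparator arm is underdosed and the trial tilted toward non-inferiority. The documents do not support that. They give neither the share of patients at 20-23 kg nor any relation between dose and cure. Purely as assumptions, a 5% share with a 10-point loss of cure moves the chloroquine rate by 0.05 x 10 = 0.5 points, and a 10% share by 1.0 point, against the 10-point margin. The opposite inference, that the flat adult dose makes up for the low band, cannot be drawn either: 620 mg is 15.1 mg/kg at 41 kg but 6.9 mg/kg at 90 kg, and no weight distribution is given.

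A reader might also take the missing child/adult boundary as part of this error. It is a separate, minor matter of clarity. Above 40 kg there is no child row, so only the adult table fits, and a child of 38 kg naturally falls in the 28-38 kg row. Doubt remains chiefly for an adult of 40 kg or less: at 38 kg the two tables give 310 or 620 mg on each of Days 0 and 1.

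**Conclusion.** The point holds for one row. For children of 20-23 kg the stated chloroquine dose is wrong, by 22.5% to 32.6% on each day and in total, and no eligible child in that row can receive it. This rests on the 155 mg tablet strength and on whole-kilogram bands; if weights up to 23.99 kg fall in the row, the shortfall reaches 35.4%. Any effect on the Day 14 comparison is confined to this band, its direction depends on a dose-cure relation that the protocol does not give, and its size cannot be worked out. It should be fixed because the comparator's dose is a figure on which a non-inferiority conclusion relies, and because correcting it is straightforward.

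**What to change.** Make one of two changes, by amendment under section 7.5, which requires notification to or approval by each IEC or IRB and, in many countries, the regulator.

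**(a) Correct the text and leave the tablets as they are.** In section 4.2.2, the Synopsis and the Introduction, give 10/10/5 mg/kg as a target and add the range delivered, as section 4.2.1 does for pyronaridine artesunate: 6.7-11.9 mg/kg on Days 0 and 1, 3.4-6.5 mg/kg on Day 2 and 16.8-29.8 mg/kg in total, lowest at 20-23 kg. Then confirm or correct the Introduction's statement that the total dose follows current practice. This discloses the low dose; it does not raise it. The cost is wording in three places and one clinical confirmation.

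**(b) Change the 20-23 kg row to 1.5/1.5/0.5 tablets.** Days 0 and 1 become 232.5/20 = 11.6 to 232.5/23 = 10.1 mg/kg, and the total 542.5/20 = 27.1 to 542.5/23 = 23.6 mg/kg (+8.5% to -5.7% against 25). Align the tablet ranges for Days 0 and 1 in section 4.2.2 (1.5 to 3) and the Synopsis (2.5 to 8 for both drugs together). State that Day 2 stays at 3.9-3.4 mg/kg because 0.5 is the nearest half tablet. This is a paediatric dose change and needs clinical agreement.

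Neither option needs repackaging: the chloroquine bottles already hold 4, 4 and 2 tablets. As a minor clarification in the same amendment, add a sentence saying which patients use the child table and which the adult table, chiefly for adults of 40 kg or less.

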**Product for Clinical Study Use ONLY**Study Reference: **SP-C-006-06**

Patient number:

Study Visit: *Day 2*Contains: *2 Tablets*

Each tablet contains:

chloroquine base 155 mg or matching placebo

Storage:

Lot No.:

Expiration date:

To be administered by Study Staff only

Sponsor: SHINPOONG PHARM. Co., Ltd., Republic of Korea

**4.2.3. Primaquine**

Primaquine will be supplied by Shin Poong Pharm Co. Ltd. Clinical trial material will be presented in an open-label manner, in high density polyethylene bottles.

The dosage to be used for adults is 15 mg primaquine on Days 28 through 42. The tablet strength to be used is 26.3 mg primaquine phosphate (equivalent to 15 mg primaquine base), which will provide a posology for adults of 1 tablet every day for 14 consecutive days, starting on Day 28 (see Attachment 4).

The dosage to be used for children is 0.5 mg/kg primaquine phosphate (equivalent to 0.3 mg/kg primaquine base) per day (see Attachment 4).

Note: Due to the risk of haemolytic anemia in G-6-PD-deficient patients, primaquine shall be administered only to patients with normal G-6-PD activity (as determined at baseline). Furthermore, for women of childbearing potential, primaquine will only be administered once a negative pregnancy test has been demonstrated.

Example Product Label for primaquine:

|                                                                                                                                                                                                                                                                                                                                                                                                                                       |
|---------------------------------------------------------------------------------------------------------------------------------------------------------------------------------------------------------------------------------------------------------------------------------------------------------------------------------------------------------------------------------------------------------------------------------------|
| 
Product for Clinical Study Use ONLY
 
Study Reference: SP-C-006-06
 
Patient number:
 
Study Visit: Day 28 through Day 42
 
Contains: 14 Tablets
 
Each tablet contains:
 
primaquine base 15 mg
 
Storage:
 
Lot No.:
 
Expiration date:
 
To be administered by Study Staff only
 
Sponsor: SHINPOONG PHARM. Co., Ltd., Republic of Korea
 |
|---------------------------------------------------------------------------------------------------------------------------------------------------------------------------------------------------------------------------------------------------------------------------------------------------------------------------------------------------------------------------------------------------------------------------------------|

